### Statistical analysis

Continuous variables will be expressed as mean, standard deviation, median, minimum, maximum, Q1, and Q3. Categorical variables will be expressed as numbers and percentages. The *t* test and Wilcoxon rank sum test will be used to compare continuous variables, and chi-square analysis/Fisher’s exact test will be used to compare categorical variables. Survival analysis will be conducted using the Kaplan-Meier method and the log-rank test. Statistical analysis will be carried out using SAS 9.2. All statistical tests are two-sided tests, and a *P* value less than or equal to 0.05 is considered as statistically significant.

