### Endpoints

The primary endpoint of this trial is 3-year disease-free survival (DFS). Secondary endpoints include 3-year overall survival (OS), postoperative complication rates, perioperative mortality rates, and rates of positive central lymph nodes (the station 3 nodes).

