### Randomization and blinding

Patients enrolled in this study will be randomly assigned into either the study group or the control group. The random numbers are generated using Statistical Analysis System (SAS) software to ensure that patients are randomly divided into two groups with an allocation ratio of 1:1. A central randomization system will be employed, and all the researchers must register at the website of the research system. When a researcher has chosen a certain patient, he/she should log on to the webpage and upload the basic information on the patient before acquiring the random grouping schemes.

All the patients are blinded to the surgical approach that they are going to receive, and will be required to sign the informed consent before being enrolled in the study. Obviously, it is impossible to blind the surgeons who will perform the surgeries. However, all the surgeon researchers will be required to limit potential co-interventions as much as possible. In addition, the result assessment will be made by independent researchers who are blinded to the surgical procedures.

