### Sample size calculation

Previous retrospective studies reported that the 3-year DFS for the D2 operation ranged from 66.7% to 82.1%; the range was 77.4% to 89.1% for the CME operation [10, 15]. We estimate that the 3-year DFS for D2 and CME will be 72.0% and 80.0% respectively in this study. We expect to detect a difference of 8% in 3-year DFS between the two groups. Thus, with a significance level of 5%, a two-sided test, and 80% power, 447 patients will be required for each group. With a drop-out rate of 20%, the required sample size is 1072 patients for both arms.

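### Stratifying the primary log-rank test by clinical T and N stage would be a modest, inexpensive gain in efficiency and robustness; the plain test as stated is valid

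*Protocol article*

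**What the plan says.** - **Endpoint** (Endpoints): "The primary endpoint of this trial is 3-year disease-free survival (DFS").
- **Test** (Statistical analysis): "Survival analysis will be conducted using the Kaplan-Meier method and the log-rank test". No strata, covariates or regression model are named, and no other test is given for DFS.
- **Stage at entry** (Study subjects, inclusion criteria): patients must have clinical T2 to T4a node-negative disease, or node-positive disease of any T category, without metastasis, as judged on CT, MRI or similar imaging. A clinical T and N must therefore exist for every eligible patient before allocation.
- **Randomisation** (Randomization and blinding): patients are "randomly divided into two groups with an allocation ratio of 1:1" through a central system, and researchers "upload the basic information on the patient before acquiring the random grouping schemes". No stratification factor is named, and the fields that make up the basic information are not listed.
- **Design target** (Sample size calculation): "We estimate that the 3-year DFS for D2 and CME will be 72.0% and 80.0% respectively in this study", an absolute gap of 8 points. The size per arm is given as follows: "with a significance level of 5%, a two-sided test, and 80% power, 447 patients will be required for each group". An allowance of 20% for loss of patients then brings the total to 1072.

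**The concern.** Eligibility spans a wide range of disease, from clinical T2 node-negative to T4a and node-positive. If clinical stage predicts DFS, a test that compares CME and D2 within stage groups has somewhat more power than one that pools all patients. It also removes the effect of any chance difference in stage mix between the arms. The article describes no stratified randomisation that would limit such a difference.

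There is a reason to settle this early. Adjustment chosen after an imbalance has been seen carries little weight. The tempting late choice, pathological N stage, would be unsound here. CME removes additional nodal tissue (For CME procedure), and the rate of positive central nodes is itself a secondary endpoint, so pathological stage can be affected by the arm. Clinical stage on imaging is fixed before allocation and does not have this problem.

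**Working it through.** **1. Reproduce the plan's figure.** Inputs from Sample size calculation: 72.0% and 80.0%, two-sided 5%, 80% power. For two proportions with pooled variance and no continuity correction, the mean proportion is 0.76 and

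n = [1.960 × √(2 × 0.76 × 0.24) + 0.842 × √(0.72 × 0.28 + 0.80 × 0.20)]² / 0.08² = (1.184 + 0.506)² / 0.0064 ≈ 446.2, which rounds up to **447 per arm**. This matches the plan.

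**2. Does the plain log-rank deliver that power?** With exponential survival the hazard ratio is ln 0.80 / ln 0.72 = 0.679. Over 3 years, 894 patients at an average event rate of 24% give 894 × 0.24 ≈ 215 events. By Schoenfeld's formula, z = √(214.56/4) × |ln 0.679| − 1.960 = 2.832 − 1.960 = 0.872, so power is **80.9%**. The stated power is met without stratification.

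**3. What does stratification add?** The inputs below are assumptions, since the documents give no prognostic hazard ratio for clinical T or N and no share of N+ or high-T patients. The simulation used 894 patients, 3 years of follow-up, marginal 3-year DFS held at 72% and 80%, 50% N+ and 25% high-T (except the last row), four T × N strata and 4,000 runs per row.

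| Assumed HR for N, T | Unstratified | Stratified | Change (points) |
|---|---|---|---|
| 1, 1 | 80.9% | 80.3% | −0.6 |
| 1.3, 1.2 | 79.4% | 80.1% | +0.7 |
| 1.5, 1.5 | 80.5% | 80.7% | +0.2 |
| 2, 1.5 | 81.0% | 82.3% | +1.3 |
| 2, 2 | 80.0% | 82.1% | +2.0 |
| 3, 2 | 80.5% | 84.8% | +4.3 |
| 4, 3 | 80.7% | 87.3% | +6.6 |
| 2, 2 (40% N+, 10% high-T) | 80.0% | 81.1% | +1.1 |

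Changes are taken before rounding. The simulation error of each power estimate is about √(0.8 × 0.2 / 4000) = 0.6 points, so the smallest changes cannot be told from zero. Under the null at hazard ratios (2, 2), the type I error is 4.5% unstratified and 4.8% stratified.

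A second set of runs used 858 patients (1072 × 0.8), 50% N+ and 20% T4. It gave 78.7% for both tests when stage is not prognostic, about +1 point at hazard ratios of 1.5, +2 near 2, and +3 at (3, 2).

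**4. Chance imbalance.** With 429 per arm and an assumed 50% N+, the standard deviation of the between-arm difference in N+ share is √(2 × 0.25 / 429) = 3.4 points. A difference of 1.96 × 3.4 ≈ 6.7 points or more, in either direction, arises in about 5% of trials. If CME receives 6.7 points more N+ patients, simulated power (stratifying on N only) is:

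| Assumed HR for N | Unstratified | Stratified |
|---|---|---|
| 1.5 | 72.6% | 78.8% |
| 2 | 68.4% | 79.7% |
| 3 | 63.3% | 81.9% |

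The mirror-image imbalance would flatter CME. Averaged over all random imbalances, the gain from stratifying on N alone is 0.1, 1.8 and 2.7 points respectively.

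**The case against.** The strongest reply is that nothing in the Statistical analysis section is wrong. An unstratified log-rank is valid under the 1:1 randomisation described, and the sample size relies on no covariates. A journal article condenses its protocol, and strata are commonly left to an analysis plan that is not shown. The benefit rests on prognostic strengths that the documents do not give, it is small in the moderate scenarios, and staging by imaging misclassifies some patients. All of this stands, and it limits the point to a recommended improvement to the one survival method the article states.

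A reader might infer more, and four such inferences are not supported:

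- **That the plain test leaves the trial underpowered.** It gives about 80.9% at 894 patients. The figures below 80% at 858 patients come from how drop-out was added to the sample size, which is a separate matter.
- **That omitting stage biases the hazard ratio towards 1.** This is mostly the difference between a marginal and a stage-conditional hazard ratio. The trial is designed around a marginal 8-point difference, and the plain comparison is not biased for that target.
- **That chance imbalance invalidates the result.** The test's type I error already allows for it. A typical imbalance is small: with 447 per arm its standard deviation is √(0.5/447) = 3.3 points, and at an N hazard ratio of 2 this moves the hazard ratio by about 0.033 × (2 − 1)/1.5 ≈ 2%, against a target of 0.68. Only the uncommon larger imbalances matter much.
- **That stratifying gains power at no cost.** The gain can be nil, and the hazard ratio changes its meaning.

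**Conclusion.** The point holds as an efficiency and robustness improvement, not as an error. The stated DFS test has no strata, although a suitable pre-randomisation factor must exist for every eligible patient.

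The expected change in power is about 0 points if clinical stage is not prognostic, 0 to 1 at hazard ratios of 1.5, about 2 at hazard ratios of 2 (nearer 1 if N+ and high-T patients are fewer), and 3 to 4 at 3 for N and 2 for T. The larger figure of 6.6 points needs hazard ratios of 4 and 3. All of these rest on assumed prognostic strengths, assumed stage shares, exponential survival and proportional hazards within strata. The power gain alone is a modest argument. Protection against an unlucky allocation, and closing off later adjustment for pathological stage, add to it.

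**What to change.** Before unblinding, pre-specify along these lines: *The primary DFS comparison is a log-rank test stratified by clinical N (N0 versus N+) and clinical T (T4 versus lower), as determined on imaging before randomisation, and by any factor used to stratify the randomisation. The hazard ratio comes from a Cox model with the same strata. Pathological stage and node count are not used for adjustment.*

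Keep the unstratified log-rank as a sensitivity analysis. Report Kaplan-Meier 3-year DFS by arm with the difference, so that the marginal 8-point target is still addressed directly. If the unseen analysis plan already says this, it need only be confirmed.

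The cost is a few sentences. No extra assessment is needed, but the sponsor should confirm that clinical T and N are held as data fields, since the article mentions only basic information. If centre turns out to be a randomisation factor, crossing it with stage would give 17 × 4 = 68 strata for about 215 events, roughly 3 per stratum, so centre would need separate thought. The remaining downside is that the hazard ratio becomes conditional on stage, for a gain that may be near zero if clinical stage is weakly prognostic.

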### Data and safety monitoring

An independent Data and Safety Monitoring Board (DSMB) including senior colorectal surgeons, biostatisticians, a research contractor, and an ethicist has been set up. DSMB members will meet before the study and every 6 months during the study. The DSMB will review elements of the study, including adverse events (AEs), drop-outs, and endpoints. If the interim results show a huge difference between the two groups that is much more than anticipated, the DSMB can stop the study early for the safety and benefit of the patients.

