## Methods/design

### Study design

This study is a superiority trial. The main objective is to investigate whether extended lymphadenectomy (CME) in laparoscopic colectomy could improve the oncological outcomes of patients with right-sided colon cancer, compared to laparoscopic colectomy with D2 lymphadenectomy.

The study design is a prospective, multicenter, randomized, two-arm, parallel-group, single-blind clinical trial. The enrolled participants with right-sided colon cancers, including cancers situated from the cecum to the right third of the transverse colon, will be divided into two groups: the laparoscopic CME group (the intervention group) and the laparoscopic colectomy with D2 dissection group (the control group).

According to the final pathological results of surgical specimens, patients with stage III colon cancer or stage II disease with unfavorable histological features will be required to undergo adjuvant chemotherapy for 6 months. The oxaliplatin-based combination regimen will be recommended.

All the patients will be followed up regularly for at least 5 years, according to the follow-up protocol recommended by the NCCN guidelines. All patients are required to undergo postoperative examinations every 4 months for the first 2 years and every 6 months thereafter until 5 years after the surgery. Signs of suspected disease relapse including local recurrence (LR) or distant metastasis (DM) will be closely observed and monitored. The schedule of this trial is shown in Table 1.

**Table 1 Tab1:** Schedule of enrollment, intervention, and assessments for the RELARC trial

	Study period										
	Enrollment	Allocation	Post-allocation								Close-out
Timepoint	–2 weeks	0	Surgery	4 months	8 months	1 year	16 months	20 months	2 years	30 months	3 years
Enrollment:											
Eligibility screen	X										
Informed consent	X										
Allocation		X									
Interventions:											
Laparoscopic D2 operation			X								
Laparoscopic CME operation			X								
Assessments:											
Disease-free survival				X	X	X	X	X	X	X	X
Overall survival				X	X	X	X	X	X	X	X
Postoperative complication			X								
Perioperative mortality			X								
Central lymph node assessment			X								

Our study is expected to last 7 years, including 4 years for recruiting patients and 3 years for follow-up.

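### The DSMB may stop for benefit on an unquantified large observed difference at six-monthly looks, while the final test keeps the full 0.05, so the 5% error rate is not guaranteed

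*Protocol article*

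**What the plan says.** Under Data and safety monitoring, the protocol article sets the frequency of review: "DSMB members will meet before the study and every 6 months during the study". The items reviewed include endpoints as well as adverse events and drop-outs. The trigger for an early stop is: "If the interim results show a huge difference between the two groups that is much more than anticipated". The section gives the purpose of such a stop as patients' safety and their benefit. It names no endpoint, threshold, direction or minimum number of events.

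Under Study design, "This study is a superiority trial", planned to last 7 years (4 of recruitment, 3 of follow-up). Under Sample size calculation, "We estimate that the 3-year DFS for D2 and CME will be 72.0% and 80.0% respectively in this study" and "Thus, with a significance level of 5%, a two-sided test, and 80% power, 447 patients will be required for each group". Under Statistical analysis, survival is compared by log-rank test, all tests are two-sided, and a P "value less than or equal to 0.05 is considered as statistically significant". No section reserves any part of the 5% for interim looks.

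**The concern.** The article does more than leave out a boundary. It states a stopping criterion of its own, and that criterion is tied to how large the observed difference is. Effect size and strength of evidence part company when events are few: a large observed effect early on may be weak evidence, while the same effect later would be strong. The only anticipated difference the article states is 8 points in 3-year DFS. No patient can have three years of follow-up at the five looks before year 3 (0.5 to 2.5 years), which are also the looks with the fewest events.

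Two things are at stake. First, if the DSMB can stop for benefit under this criterion and the trial otherwise tests at 0.05, the overall chance of a false positive is 5% plus an amount nobody can state. Second, a trial stopped because the observed effect passed a high mark reports an effect at or beyond that mark, whatever the true effect is.

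**Working it through.** **1. The plan's own figure.** Two proportions, pooled variance, two-sided 0.05, 80% power, p1 = 0.72, p2 = 0.80, mean 0.76:

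n = [1.960·√(2·0.76·0.24) + 0.842·√(0.72·0.28 + 0.80·0.20)]² / 0.08² = [1.960·0.6040 + 0.842·0.6013]² / 0.0064 ≈ 446.2, rounded up to **447 per arm**.

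The stated 447 is reproduced exactly as a single-analysis calculation, so it contains no allowance for interim looks. With exponential DFS the design effect is HR = ln 0.80 / ln 0.72 = 0.679.

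**2. Number of looks.** Six-monthly reviews over 7 years give up to 13 interim looks (0.5 to 6.5 years) before a final analysis at year 7.

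**3. Why effect size alone is not evidence.** With 1:1 allocation the standard error of log HR is about 2/√d for d events. An observed HR of 0.5 (|log HR| = 0.693) means:
- d = 20: z = 0.693/0.447 = 1.55, two-sided P ≈ 0.12
- d = 50: z = 0.693/0.283 = 2.45, P ≈ 0.014
- d = 100: z = 0.693/0.200 = 3.47, P ≈ 0.0005

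The same observed effect is weak or compelling evidence depending on an event count that the criterion leaves open.

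**4. Simulation under no effect.** Assumptions: 447 per arm, uniform accrual over 4 years, exponential DFS with the same 3-year rate in both arms, no drop-out, 13 interim looks plus a final log-rank test at year 7, 6,000 trials. An error is an interim stop or final P ≤ 0.05, in either direction. Monte Carlo standard error near 5% is about 0.3 points. With a 72% null, mean events at 0.5, 1.0, 1.5, 2.0, 2.5 and 3.0 years are 3, 12, 26, 46, 70 and 99. The article does not define *huge*, so each row is an assumed reading.

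| Interim stop if | 72% null | 76% null |
|---|---|---|
| No interim stop (final test only) | 5.0% | 4.4% |
| Log-rank P ≤ 0.001 | 5.4% | 4.6% |
| 3-year Kaplan-Meier gap ≥ 16 points* | 5.1% | 4.5% |
| HR beyond 0.5, at least 50 events | 5.6% | 5.0% |
| 3-year gap ≥ 12 points* | 6.3% | 5.3% |
| 3-year gap ≥ 10 points* | 9.3% | 7.3% |
| HR beyond 0.60, at least 50 events | 9.4% | 9.0% |
| HR beyond 0.5, at least 20 events | 12.2% | 12.0% |
| HR beyond 0.60, at least 20 events | 25.4% | 26.3% |

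*Applied at looks from year 3.5. Compare rows within a column, because the 76% column starts from 4.4%.

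A separate simulation with 1072 patients, a 76% null and 12 interim looks plus the final gave 12% for HR beyond 0.5 with at least 20 events, 5.5% with at least 50, and 5.2% for P ≤ 0.001. Another run at that sample size gave 6.3% and 5.0% for gaps above 10 and 12 points. The Kaplan-Meier rows therefore shift with sample size and null rate, whereas the contrast between few and many events is stable.

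**5. Exaggeration.** If the stop requires HR beyond 0.5, every trial stopped for benefit reports an HR below 0.5, even if the truth is the design value of 0.679.

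**The case against.** The strongest reply is that boundaries and look timing usually sit in an analysis plan or DSMB charter, that this is a condensed article, and that the DSMB includes biostatisticians. A boundary may well exist there, and its absence from the article would be no fault. But the article states a criterion of its own, based on magnitude, next to an unadjusted 0.05. An unseen charter does not correct that sentence.

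The reply is right on several further points, which limit the conclusion:
- A reader might infer an error rate of about 24 to 26%, the result of stopping at any look with P ≤ 0.05. The text does not support this. It asks for a difference well beyond the anticipated one, and from about 103 events (around year 3) P = 0.05 corresponds to an effect smaller than the design effect. Crossings in both directions are also counted; counting only those favouring CME gives about 11.6% against a nominal 2.5%.
- A reader might infer that differences are judged visually, or that a comparative DFS test is run at every meeting. The article says neither. The difference could also concern complications or perioperative mortality, which are secondary endpoints.
- The highest effect-size figures depend on looks with few events, and it is speculative that this DSMB would act on them.
- A reader might infer that the final P value would be unacceptable. If no look can lead to a stop for benefit, the final test alone has about 5% error. The problem is conditional on such a stop.

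**Conclusion.** The concern holds in a limited form: the 5% level is not guaranteed, but the article does not show that it is grossly inflated. Under strict readings the overall two-sided error stays at about 5 to 5.5%. Under looser effect-size readings, especially those allowing a stop on few events, it reaches about 9 to 12%, and more if HR 0.60 on 20 events were accepted. The article does not determine where in this range the trial lies. The figures rest on exponential DFS, uniform accrual, no drop-out, DFS as the endpoint compared, and a comparison at every six-monthly meeting. An exaggerated effect estimate after a stop follows from any magnitude-based trigger. The point deserves a change to the text but does not undermine the design.

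**What to change.** Replace the sentence with one of two statements.

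(a) A pre-set efficacy boundary on DFS, for example a Haybittle-Peto rule: a stop for benefit is considered only if the two-sided log-rank P < 0.001 at one or two pre-set fractions of the planned events, with the final test at 0.05. With two looks the overall error cannot exceed 0.05 + 2 × 0.001 = 5.2%; applied at all 13 looks it was 5.4% in simulation. The article states no planned number of events, so the count on which the fractions are based must be given as well. An alpha-spending boundary with a matching final level would serve equally.

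(b) A statement that DSMB reviews carry no stop for benefit.

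Under either, describe the review for harm separately. The DSMB may continue to see endpoints every six months. If a charter already holds a boundary, state it here or refer to it.

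The cost is protocol or charter wording. Under the Haybittle-Peto option the final level stays at 0.05, so the loss of power is negligible; alpha-spending lowers the final level slightly.

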## Discussion

In the past 30 years, the development of surgery for colorectal cancer has been unbalanced. The surgical procedure for colon cancer is relatively unchanged, but the surgical treatment of rectal cancer has been constantly evolving. Contributing factors to this situation include the double-stapling technique, the principle of total mesorectal excision (TME), the 2-cm distal margin, neoadjuvant therapy, and other new technologies.

The transformation of traditional open surgery to minimally invasive surgery has become an inevitable trend. Some high-level clinical studies have shown that laparoscopic surgery and open surgery did not have significant differences in the long-term oncological outcomes or the short-term effect for colorectal cancer [16–18]. The 2015 NCCN guidelines for colon cancer advocated laparoscopic colectomy to experienced surgeons. The incidence of right colon cancer accounts for more than 50% of colon cancer occurrence. Right colectomy is relatively consistent, and open right colectomy is even considered to be the entry procedure for colorectal specialists. The anatomical layers in laparoscopic right colectomy, however, are more complicated compared to other parts of colon cancer surgery by the laparoscopic approach, and vascular variation in this region is common. Therefore, the difficulty of laparoscopic right colectomy is greater than that of the open procedure [5]. Neither the NCCN nor the ESMO guidelines have clearly defined the extent of lymphadenectomy for a radical right colectomy. Therefore, the key steps of laparoscopic right colectomy are still controversial.

The concepts of D3 dissection and CME developed in different eras and different countries. The concept of CME historically originated from TME, which emphasized dissection along the embryologic plane and ligation of the supplying vessels at their origins. The other difference between D3 dissection and CME is the longitudinal resection (longitudinal margin of 10 cm versus right hemicolectomy), the latter technique bring a more extensive longitudinal removal. In the present study, all procedures require sharp dissection strictly following the embryologic plane and are basically a right hemicolectomy, which is different from D3 dissection. For cancer of the hepatic flexure and right third of the transverse colon, more extensive resection of the transverse colon in the proximity of the splenic flexure is recommended.

In the past 30 years, similar disputes or innovations for gastrointestinal surgeries include the principle of TME for rectal cancer, the extent of lymph node dissection for gastric cancer, and lateral lymph node dissection for rectal cancer, etc. The principle of TME received general approval immediately after it came out because it did not increase the difficulty of the operation and achieved less bleeding, although it was not confirmed by randomized controlled studies. However, other issues, including D2 or more extended lymphadenectomy for advanced gastric cancer [19, 20] and the necessity of lateral lymph node dissection for rectal cancer, were controversial [21]. Eventually, some advanced studies of evidence-based medicine settled the arguments and formed the current guidelines. The concept of CME originated from TME, but whether it can achieve the same acceptance as TME still needs to be verified in practice.

